### Statistical analysis and sample size calculation

#### Sample size estimation

Data from other studies using EORTC QLQ-C30 suggest a standard deviation of less than 25 for a difference between the repeated measurements, and a group difference of 10 for clinical relevance [31].

With a risk of type I error of 0.05 and type II error of 0.10, 133 patients are required in each arm. In order to allow for a dropout rate of approximately 10% each arm will enroll 150 patients for a total of 300 patients.

### Plan of analysis

#### Questionnaire data

Analyses will be made using the statistical package STATA, latest version (StataCorp, Texas, USA). The primary analysis will be based on the intention-to-treat principle. If the proportion of lacking answers is higher than 5%, we will use multiple imputations in the primary analysis with the following variables: age, gender, diagnosis, cancer stage, and WHO performance score. The questionnaire data will be transformed according to their respective scoring manuals [32, 24].

Multiple regressions will be applied, since despite the randomized design there may be imbalance between the two arms. We will adjust for “the primary problem” and WHO performance score.

Wilcoxon and Chi2 will be used to investigate whether there are differences between the two groups in relation to the following variables that may be of prognostic importance: gender, age, cancer stage, primary diagnosis, marital status, and educational background. If a significant group difference is found, the respective variable will be included in a sensitivity analysis.

In the analyses we combine the data from the three questionnaires by constructing an AUC using a weighted average of the change from baseline to the 6 and 12-week follow-up. A model for longitudinal data and repeated measurements in the multivariate analysis is applied as a subsequent sensitivity analysis.

Since the primary outcome measure “the primary problem” consists of 13 possible choices, we will also perform separate analyses of patients with the same primary problem.

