### Enrollment procedure and baseline data collection

Eligible patients are informed about the project by a doctor or nurse in the outpatient clinic.

Patients who have signed the informed consent form are asked to complete a baseline questionnaire. Baseline characteristics of the patient (WHO performance status, diagnosis, age, gender, time of primary diagnosis, cancer stage, marital status, and educational background) are registered. Randomization is subsequently performed by the clinical trial unit using a randomization list from randomizer.org [20]. Patients are randomized 1:1 to the intervention or control group with no further stratification used during randomization. The randomization list is blinded from anyone involved in informing potential study participants.

If a patient does not wish to participate, the reason is noted, if possible, and the following characteristics are registered anonymously; diagnosis, age, gender, WHO performance status, cancer stage, marital status and educational background.

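### The 5% trigger for multiple imputation has no unit or denominator, so at the planned 10% dropout it may or may not fire, and nothing is stated for patients without a full AUC when it does not

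*Protocol article*

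**What the plan says.** Under Questionnaire data in the Plan of analysis, the protocol article states: "The primary analysis will be based on the intention-to-treat principle". The next sentence sets the rule for missing data: "If the proportion of lacking answers is higher than 5%, we will use multiple imputations in the primary analysis". The imputation variables it lists are age, gender, diagnosis, stage and performance score. The list contains no questionnaire score.

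The same section describes the outcome: "In the analyses we combine the data from the three questionnaires by constructing an AUC", as a weighted average of the changes from baseline to weeks 6 and 12. A longitudinal repeated-measures model is planned, but only as a later sensitivity analysis.

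Under Sample size estimation, dropout is counted in patients: "In order to allow for a dropout rate of approximately 10% each arm will enroll 150 patients". Under Enrollment procedure and baseline data collection, the baseline questionnaire comes before randomisation.

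**The concern.** The trigger is worded in answers, while the outcome and the dropout allowance are both counted per patient. A patient who misses only week 12 lacks one questionnaire of three, yet has no full AUC. If the baseline forms are in the denominator, they are nearly all complete and pull the share down. The same data can then fall on either side of 5%, depending on a denominator that the text does not fix.

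At or below 5%, the article states no way of keeping a patient without a full AUC in the primary analysis. A regression on an outcome that cannot be computed omits the patient by default. In newly diagnosed advanced cancer, those who stop answering are plausibly those who deteriorate, so leaving them out risks bias in the primary comparison.

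**Working it through.** **The plan's own figure.** The inputs are "a standard deviation of less than 25 for a difference between the repeated measurements, and a group difference of 10 for clinical relevance" and "With a risk of type I error of 0.05 and type II error of 0.10, 133 patients are required in each arm", with 1:1 allocation.

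- Two-sided normal approximation: n = 2 × (1.960 + 1.282)² × 25² / 10² = 131.3, so 132 per arm.
- The t-test version gives 132.3, so 133. The stated figure is reproduced. A one-sided test would give 108 and does not match.
- Dropout allowance: 133 / 0.90 = 147.8, so 148; the plan enrols 150. The dropout implied by 133 of 150 is 1 − 133/150 = 11.3%.

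**The trigger at the planned dropout.** Let d be the proportion of patients who drop out, and f the share of them lost before week 6. The document does not give f, so it is an assumption, shown from 0 to 1. Further assumptions are that baseline is complete, that whole questionnaires are lost, that dropouts do not return, and that nothing else is missing. The lacking share is then:

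- by patients without a full AUC: d
- by follow-up questionnaires: d(1 + f)/2
- by all three questionnaires: d(1 + f)/3

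With d = 10% (30 of 300 patients):

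| Share lost before week 6 (f) | By patients | By two follow-ups | By three questionnaires |
|---|---|---|---|
| 0 | 10% | 5.0% | 3.3% |
| 0.5 | 10% | 7.5% | 5.0% |
| 1 | 10% | 10% | 6.7% |

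The rule needs a share above 5%, so exactly 5.0% does not fire it.

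- By patients it always fires.
- By follow-up questionnaires it fails only if every dropout comes after week 6.
- By three questionnaires it fails if half or more of the dropouts come after week 6 (break-even f = 3 × 0.05/0.10 − 1 = 0.5).

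With d = 11.3%, the follow-up count runs from 5.7% to 11.3% and always fires. The three-questionnaire count runs from 3.8% to 7.6% and fails if f is below about 0.32.

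**Consequence if it does not fire and dropouts are omitted.** At d = 10%, 30 of 300 patients are lost, leaving 135 per arm if losses are equal. Power for a difference of 10 with SD 25 is then 0.908, against 0.903 at 133 per arm. The sample size already allows for this loss.

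**The case against.** Five points can be made against the concern.

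- **The unit.** A reader might infer that the trigger counts answers and not patients, so that the planned dropout would go unimputed. The text does not establish this. Read as patients lacking the primary outcome, 10% exceeds 5% and imputation is used. What stands is that the unit is undefined.
- **The boundary.** The 5.0% case with three questionnaires is 45 of 900 forms, and one more missing form fires the rule. Not firing mostly requires counting baseline and having mainly late dropout. This makes the failure less likely. It does not exclude it, since no timing of dropout is given and the plan itself speaks of three questionnaires.
- **Exclusion.** A reader might also infer that the plan contradicts intention-to-treat by prescribing a complete-case analysis. No such rule is written. A partial AUC from week 6 alone is conceivable, and the longitudinal model could use a lone week-6 score. But the partial AUC is not described, and the model is not the primary analysis.
- **Open-label choice of method.** The section on other statistical and methodological considerations says the primary data analysis is done blinded, with coded numbers. A threshold fixed beforehand and applied blind is not chosen on the treatment effect. This largely answers that worry.
- **Missing detail.** A journal article may leave the counting unit to a fuller document, and the undefined unit alone would not be a finding. The switch itself, however, is stated here and governs the primary method.

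**Conclusion.** The concern holds in a limited form. The article fixes a data-dependent switch for the primary method whose outcome at the planned dropout depends on an undefined count: 10% by patients, 5.0% to 10% by follow-up questionnaires, 3.3% to 6.7% by all three. On some of these readings imputation is not used, and up to about 30 of 300 patients could be left out of an analysis described as intention-to-treat.

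This rests on assumed dropout timing, on losses of whole questionnaires only, and on omission being the default where no handling is stated. The document supports neither a claim that these patients will be dropped nor a claim of lost power. The harm is possible bias, whose size cannot be computed from the document, and an indeterminate primary method. The point should be fixed, but it does not undermine the design.

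**What to change.** Delete the 5% trigger. State that the primary analysis includes all randomised patients and uses all observed scores, with multiple imputation whatever the amount missing.

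Three additions are needed for this to work:

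- Add the baseline score and the available week-6 and week-12 scores of the patient's chosen scale to the imputation variables. With the present list, imputed values would ignore the scores that dropouts did give, so removing the trigger alone would not deal with the possible bias.
- State how deaths before week 12 are treated in the primary outcome, since imputing for every randomised patient raises that question.
- Report a complete-case analysis as a sensitivity analysis.

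The cost is a few sentences in the analysis plan and slightly more analysis work. No new data are needed. The article reports that recruitment was still under way at 68% of the target.

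### The listed imputation variables for the primary analysis omit randomised arm, so imputed values shrink the treatment effect by roughly the missing fraction; scores and primary problem are also unlisted

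*Protocol article*

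**What the plan says.** Under Plan of analysis, Questionnaire data, the Protocol article makes multiple imputation part of the primary analysis on a condition: "If the proportion of lacking answers is higher than 5" percent, then "we will use multiple imputations in the primary analysis with the following variables: age, gender, diagnosis, cancer stage, and WHO performance score". All five are baseline characteristics. No other section adds to the list.

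The outcome to be imputed is defined under Measurement instruments. It is the between-arm difference in change from baseline to a weighted average of the 6- and 12-week scores (AUC), on the scale that the patient chose as the primary problem. The analysis is a multiple regression: "We will adjust for “the primary problem” and WHO performance score". Under Sample size estimation, the article plans for loss: "In order to allow for a dropout rate of approximately 10% each arm will enroll 150 patients".

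**The concern.** An imputation model should contain at least the variables of the analysis it serves. Two of those are not listed here: arm, which is the contrast being estimated, and the primary problem, which decides which scale is scored. The patient's own baseline score and other follow-up score, which are likely to be the best predictors of a missing score, are not listed either.

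The omissions have different consequences.

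- **Arm.** Given the five covariates, a missing intervention patient and a missing control patient receive values from the same mixed distribution. The imputed part of the data set then carries no treatment effect, and the primary estimate is diluted.
- **Baseline score, other follow-up score, primary problem.** Precision is lost and the imputation model no longer matches the analysis model. The missing-at-random assumption is also weaker than it needs to be.

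At stake is the size of the primary estimate, and with it the power to detect the 10-point difference that the trial was designed around.

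**Working it through.** **1. The plan's own figure.** Inputs from Sample size estimation: SD 25 (given as less than 25), difference 10, type I error 0.05, type II error 0.10.

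n per arm = 2 × (1.960 + 1.282)² × 25² / 10² = 131.3, so 132 by the normal approximation. The t-based calculation gives power 0.8993 at 132 and 0.9015 at 133, which reproduces the stated 133 for a two-sided test. With 10% dropout, 133 / 0.90 = 147.8, so 148, rounded up to 150. The sample size is sound.

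**2. Effect of leaving out arm.** Let the control mean be μ, the true difference δ, the allocation 1:1 and the missing fraction m in each arm, unrelated to outcome. The observed data pooled over arms have mean μ + δ/2, so that is the expected imputed value in both arms.

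- Intervention mean: (1 − m)(μ + δ) + m(μ + δ/2)
- Control mean: (1 − m)μ + m(μ + δ/2)
- Difference: δ(1 − m)

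With δ = 10, this is 9.5, 9.0, 8.0 and 7.0 at m = 5%, 10%, 20% and 30%. With δ = 0 it is 0, so no false effect is created; a real one is understated.

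**3. Simulation.** 150 per arm, δ = 10, SD 25, 20 imputations combined by Rubin's rules, 1,500 trials per row. Two inputs are assumptions: data missing completely at random, and listed covariates explaining 10% of outcome variance. Only the 10% row corresponds to a dropout rate in the article.

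| Missing | List as written: estimate, power | Arm added: estimate, power | Complete cases: estimate, power |
|---|---|---|---|
| 5% | 9.6, 90% | 10.1, 92% | 10.1, 92% |
| 10% | 9.0, 88% | 10.0, 92% | 10.0, 91% |
| 20% | 7.9, 74% | 9.9, 88% | 9.9, 87% |
| 30% | 6.9, 56% | 9.9, 83% | 10.0, 82% |

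In this setting the listed model does worse than no imputation: 150 × 0.90 = 135 completers per arm still exceed the required 133.

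Power depends on the SD. With an SD of the AUC change of about 22, power at 10% missing is 93% with the list as written and 97% with arm added. The estimates are almost the same (9.1, 8.0 and 6.8 at 10%, 20% and 30% missing).

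**4. One visit missed.** If scores are imputed visit by visit, the loss is δ × (visit weight) × (fraction missing at that visit). The article does not give the weights. For 10% missing at week 12 only, the loss is 10 × 0.5 × 0.10 = 0.5 points with equal weights, or 10 × (1/3) × 0.10 = 0.33 points with a week-12 weight of one third. With equal weights, 10% missing at week 6 and 20% at week 12, the estimate is 10 × (1 − 0.05 − 0.10) = 8.5; simulation gave 8.5.

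**5. Effect of leaving out the baseline score.** With arm in the model and dropout depending on baseline equally in both arms (about 21% missing), the estimate was 9.96 without baseline and 9.97 with it: no bias. When dropout was made to depend on baseline differently by arm (about 20% missing), it was 11.9 without baseline and 9.9 with it. That figure rests on one assumed dropout pattern and is illustrative only.

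**6. Will the 5% trigger be reached?** It counts lacking answers; the 10% counts patients. If lacking answers are counted over all three questionnaires, 10% of patients missing both follow-ups gives 0.10 × 2/3 = 6.7%, above the trigger. Missing week 12 only gives 0.10 × 1/3 = 3.3%, below it.

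**The case against.** - **The list may not be exhaustive.** The sentence does not say that only these variables are used. They could be auxiliary predictors added to the variables of the analysis model, with detail left to a fuller plan. This is possible, but the article does not say so. It names a specific list for the primary analysis, and an analyst who follows it would bias the result. If the wider model was meant, one sentence settles it.
- **A check exists.** A longitudinal repeated-measures model is planned as a sensitivity analysis. It could expose a discrepancy, but it does not repair the primary estimate.
- **Blinding.** The primary data analysis is to be blinded with coded numbers (Other statistical and methodological considerations). A coded arm label can enter the imputation without revealing allocation.
- **The loss at the planned dropout is modest.** This stands: about 1 point at most at 10%. The 20% and 30% rates are assumptions.

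Three stronger readings are tempting and not supported. A reader might infer that all four omissions pull the effect to zero; only the omission of arm does. A reader might infer that omitting baseline biases the effect whenever dropout depends on severity; step 5 shows bias only when that dependence differs by arm, and nothing in the article indicates that it will. A reader might infer that imputation is bound to be used because 10% exceeds 5%; step 6 shows that the two percentages measure different things.

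**Conclusion.** The point holds as a defect in a stated rule of the primary analysis. Taken as written, the list shrinks the treatment effect by roughly the missing fraction of the AUC: from 10 to about 9 points at the planned dropout if both follow-ups are missing, less if one visit is missed, and to about 8 or 7 at assumed missingness of 20% or 30%. At the design SD of 25, simulated power at 10% missing is 88% against 92% with arm included, which is below the 90% target; at a smaller SD it stays above the target.

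These sizes assume similar missingness in both arms, unrelated to outcome, and covariates balanced by randomisation. If missingness differs by arm but is otherwise random, the factor 1 − m becomes the harmonic mean of the two completion rates. For example, 5% and 15% missing give 2 × 0.95 × 0.85 / (0.95 + 0.85) = 0.897, close to 0.90.

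The other three omissions are a matter of precision and consistency with the analysis model, with bias only under the arm-specific dropout described above. Imputation is likely to be triggered, but this is not certain. No error is shown in the 5% threshold itself.

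**What to change.** Replace the variable list with a sentence to this effect: missing 6- and 12-week scores will be imputed with randomised arm as a predictor (or separately by arm, using a coded arm label), together with the baseline and other follow-up score of the chosen scale, the primary problem, age, gender, diagnosis, cancer stage and WHO performance score; the AUC will be derived after imputation.

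The 5% trigger need not change. The cost is one sentence in the plan. All the variables are already collected, and by the Time plan recruitment stood at 68% with the analyses still to be completed, so at that stage the change could be made before results were known.

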The primary outcome measure is the difference between the intervention and control groups in the change from baseline to the weighted average at the six and 12-week follow-up measured as area under the curve (AUC) of the EORTC QLQ-C30 scale/category chosen by the patient (e.g., if pain was designated as ‘primary problem’, the primary outcome is based on the EORTC QLQ-C30 pain scale). If a patient has ticked the box “none of the above” and hence has not chosen any of the 12 scales/categories, the primary outcome measure for this patient will be change in health related QoL corresponding to the “Global health status/QoL”-scale in EORTC QLQ-C30. This way of devising and analyzing an individualized trial outcome has previously been motivated and elaborated, although in the previous study the patients did not select the outcome measure [29, 30]. The expanded EORTC scales (see above) will be used in the primary outcome; the traditional EORTC QLQ-C30 scales will be used in a secondary analysis.

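### The primary regression analyses change from baseline without the baseline score as a covariate, which costs precision and over-corrects chance baseline imbalance

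*Protocol article*

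**What the plan says.** Under Questionnaire data, the article describes the analysis variable as "constructing an AUC using a weighted average of the change from baseline to the 6 and 12-week follow-up". The section on measurement instruments defines the primary outcome in the same way, on the expanded EORTC QLQ-C30 scale that matches the patient's chosen problem. Patients who choose none of the 12 problems are analysed on the global health status/QoL scale.

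The reason given for a regression is: "Multiple regressions will be applied, since despite the randomized design there may be imbalance between the two arms". Its covariates are then named: "We will adjust for “the primary problem” and WHO performance score". Elsewhere in the article the primary problem means the category the patient picks, with 13 possible choices. It is not a score.

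The variables tested for group differences, which can enter only a sensitivity analysis, are "gender, age, cancer stage, primary diagnosis, marital status, and educational background". No questionnaire score is among them. On the longitudinal model the article says: "A model for longitudinal data and repeated measurements in the multivariate analysis is applied as a subsequent sensitivity analysis". It does not state how that model treats baseline. Allocation is 1:1 with "no further stratification used during randomization".

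**The concern.** The starting value of the chosen scale is the measured variable that bears most directly on a change outcome. It is recorded before randomisation, yet it enters the primary model only by subtraction. Subtracting baseline is not the same as adjusting for it. Subtraction assumes that each point of baseline carries over fully to follow-up, while a regression estimates how much does. If the true slope is below 1, the change score keeps avoidable variance. It also credits the arm that happened to start worse with improvement that is only regression to the mean.

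Two things are at stake: the precision of the primary comparison, and how closely the single realised estimate reflects the treatment effect when the arms differ at baseline by chance. The category term does not solve this. It removes average differences between scales but leaves differences between patients on the same scale. The plan's stated purpose for the regression, dealing with imbalance, is thus not well served for the variable where imbalance matters most. The same applies to the planned separate analyses by primary problem, where groups are small and chance imbalance is larger.

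**Working it through.** **1. The plan's own figure.** Inputs from the sample size section: difference 10, SD 25 (stated as an upper bound), type I error 0.05 (sidedness not stated; two-sided reproduces the figure), power 0.90.

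n per arm = 2(1.960 + 1.282)² × 25²/10² = 131.3, rounded up to 132. The t-test version gives 132.3, rounded up to 133, as stated. Then 133/0.90 = 147.8, so 148, and the plan enrols 150. Power of the plain change score at 133 per arm is 90.4%. The sample size is not in error.

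**2. Assumptions needed for the comparison.** The article does not give the correlation between assessments, so ρ = 0.3, 0.5 and 0.7 are used. Also assumed: equal variance s² at all three assessments, the same ρ between any two of them, and AUC weights of 2/3 (week 6) and 1/3 (week 12). Those weights follow from the trapezoid rule on changes at weeks 0, 6 and 12: 6·c₆/2 + 6·(c₆ + c₁₂)/2 = 6c₆ + 3c₁₂, a ratio of 2:1.

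**3. Residual variance.**

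- Change score: s²[w₁² + w₂² + 2w₁w₂ρ + 1 − 2ρ] = s²(14/9)(1 − ρ)
- Baseline-adjusted: s²[w₁² + w₂² + 2w₁w₂ρ − ρ²] = s²(1 − ρ)(5/9 + ρ)
- Ratio, adjusted to change: (5 + 9ρ)/14

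If a single change has SD 25, then s² = 625/[2(1 − ρ)]. The change-AUC variance is then 625 × 7/9 = 486.1, which is SD 22.0 at every ρ.

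| ρ | Ratio | Variance reduction | Adjusted SD (from 22.0) |
|---|---|---|---|
| 0.3 | 0.550 | 45% | 16.4 |
| 0.5 | 0.679 | 32% | 18.2 |
| 0.7 | 0.807 | 19% | 19.8 |

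The ratio does not depend on which quantity is given SD 25. If the AUC change itself has SD 25, the adjusted SD is 18.5, 20.6 or 22.5, and 90% power needs 73, 90 or 107 per arm. With equal weights for weeks 6 and 12 the reductions are 47%, 33% and 20%. With a single follow-up the ratio is (1 + ρ)/2, and the reductions are 35%, 25% and 15%.

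**4. Effect of a chance imbalance.** If the arms differ by d at baseline, the follow-up difference is expected to carry ρd, and the change score subtracts d. The estimate moves by ρd − d = −(1 − ρ)d, which favours the arm that started worse.

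| ρ | s | SE of baseline difference, s√(2/133) | Shift at 1 SE | Shift at d = 5 |
|---|---|---|---|---|
| 0.3 | 21.1 | 2.59 | 1.81 | 3.5 |
| 0.5 | 25.0 | 3.07 | 1.53 | 2.5 |
| 0.7 | 32.3 | 3.96 | 1.19 | 1.5 |

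These shifts are in points, against a target difference of 10.

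**5. Sensitivity to restricted baseline variance.** The variance saved equals baseline variance × (1 − slope)². Take slope 0.5. With full baseline variance, in units of s², the adjusted variance is 0.528 and the saving is 0.25, so the reduction is 0.25/0.778 = 32%. If the baseline SD is 0.7 of the follow-up SD in the unselected population (assumed), the saving is 0.49 × 0.25 = 0.1225 and the reduction is 0.1225/(0.528 + 0.1225) = 19%.

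**The case against.** The strongest reply is that this concerns efficiency and that the trial does not need the gain. That largely stands. The change-score analysis is unbiased over repeated randomisations and keeps its type I error. Power is 90.4% at SD 25. If 25 is the SD of a single change, the AUC change has SD 22.0 and power at 133 per arm is about 96% without any adjustment. A reader who infers that the primary analysis is invalid or underpowered goes beyond what the article supports.

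A reader might also infer that baseline imbalance is left uncorrected. It is not: baseline is subtracted with slope 1, so the error is over-correction. For a typical imbalance of 1 SE the shift is 1.2 to 1.8 points.

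It is also tempting to say that baselines are extreme and regression to the mean strong, because patients pick the problem they most want help with. The article gives no data on this. Patients choose by need for help, not by highest score, and may join without feeling a need for the intervention. Strong selection would also restrict baseline variance and so reduce the gain (step 5). The percentages further ignore any variance that the primary-problem term already absorbs.

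Two defences do not stand. Adjusting for the primary problem cannot readily be read as adjusting for its score, since the article uses the term for the category. And because the covariates are named, this is a stated choice, not a detail left to an unseen SAP. The longitudinal sensitivity model may treat baseline better, but the article does not say so, and it is not the primary analysis.

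**Conclusion.** The point holds as a matter of precision and conditional bias. The named covariates omit the baseline score of the chosen scale, and a change score without that covariate is less precise than baseline-adjusted regression whenever the slope of follow-up on baseline differs from 1. Under equal variances, weights of 2/3 and 1/3 and ρ of 0.3 to 0.7, adjustment would lower residual variance by roughly 19–45%. The true gain could be smaller, for the reasons given above. A 5-point chance imbalance would move the estimate by 1.5 to 3.5 points over the same range of ρ, against a target of 10. The analysis stays valid, and the sample size reproduces. The change is a worthwhile improvement to the primary model, not the repair of an invalid one.

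**What to change.** Before analysis, add to the primary regression the baseline score of the patient's chosen expanded scale, or of global health status/QoL for patients who chose none of the listed problems. Score all scales in a common direction first, so that one slope has one meaning. In the secondary questionnaire analyses, including HADS, add each outcome's own baseline score in the same way. If multiple imputation is used, carry the same score into the imputation model so that it matches the analysis model.

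The survival and economic sections refer back to the questionnaire covariates, so the revised wording should say whether the added score is meant to apply there too.

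The baseline questionnaire is completed before randomisation, so no new data are needed. With 68% of patients enrolled when the article was written and the analyses still to come, the cost is a documented change to the analysis wording, made before the outcome data are compared between arms.

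### Covariates enter the sensitivity analysis only when a baseline test between randomised arms is significant, so chance imbalance rather than prognostic strength decides the model

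*Protocol article*

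**What the plan says.** All of this is in the Protocol article, mostly under Plan of analysis, Questionnaire data.

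- **Reason for adjusting:** "Multiple regressions will be applied, since despite the randomized design there may be imbalance between the two arms".
- **Main model:** "We will adjust for “the primary problem” and WHO performance score". These two covariates do not depend on any test.
- **Further candidates:** "Wilcoxon and Chi2 will be used to investigate whether there are differences between the two groups" for six "variables that may be of prognostic importance: gender, age, cancer stage, primary diagnosis, marital status, and educational background".
- **Entry rule:** "If a significant group difference is found, the respective variable will be included in a sensitivity analysis". The article gives no significance level for these tests.
- **Allocation** (Enrollment procedure and baseline data collection): "Patients are randomized 1:1 to the intervention or control group with no further stratification used during randomization".
- **Imputation:** if more than 5% of answers are missing, the imputation model uses age, gender, diagnosis, cancer stage and WHO performance score, with no preliminary test.
- **Other endpoints:** the Survival and Economic consequences sections refer back to the covariates of the questionnaire analysis without listing them.

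**The concern.** Under randomisation a baseline difference between arms is a chance difference. A significance test of it examines a null hypothesis already known to be true, and its p-value says nothing about whether the variable predicts the symptom score. Adjustment matters when a variable predicts outcome, and most of all when it is also imbalanced to a degree that matters. The rule looks only at the p-value of the imbalance.

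Two things follow. A variable unrelated to outcome has the same chance of entering as a strong predictor. And a strong predictor whose imbalance is material but falls short of significance is left out. The plan's stated reason for adjusting is possible imbalance, so the sensitivity analysis is the natural place to show that the result survives adjustment for diagnosis, stage and age. As written, it will usually not contain them.

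**Working it through.** **The plan's own figure.** The sample size rests on "a standard deviation of less than 25 for a difference between the repeated measurements, and a group difference of 10 for clinical relevance", and "With a risk of type I error of 0.05 and type II error of 0.10, 133 patients are required in each arm".
- Normal approximation, two-sided: 2·(1.960 + 1.282)²·25²/10² = 131.4, so 132 per arm.
- The t-based calculation gives 132.3, so 133. The plan's figure is reproduced.
- 133/0.90 = 147.8, so 148, close to the 150 planned. Baseline adjustment plays no part here, so the sample size does not depend on this point.

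**Chance of selection.** Inputs: six candidates (document) and test level α (not in the document; 0.05 assumed, 0.01 to 0.10 shown). Under randomisation each is selected with probability α. With independent tests, P(at least one) = 1 − (1 − α)⁶.

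| α | P(at least one enters) | P(none enters) | Expected number (6α) |
|---|---|---|---|
| 0.01 | 5.9% | 94.1% | 0.06 |
| 0.05 | 26.5% | 73.5% | 0.30 |
| 0.10 | 46.9% | 53.1% | 0.60 |

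Independence is an approximation; gender and diagnosis, for instance, are related when prostate and gynaecological cancers are included. Whatever the dependence, at α = 0.05 P(at least one) lies between 0.05 (all tests coincide) and 6 × 0.05 = 0.30 (no two ever significant together).

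**Imbalance that goes unadjusted.** Take one category at an assumed 40% prevalence (not in the document), 150 per arm.
- Difference needed for p < 0.05: 1.96·√(0.4·0.6·2/150) = 1.96 × 0.0566 = 0.111, about 11 percentage points.
- A split of 45% against 35% gives z = 0.10/0.0566 = 1.77, p = 0.08, and the variable stays out.

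The planned test of diagnosis would have more categories, since Study design lists seven tumour groups. With seven groups (6 degrees of freedom) and the other six equally sized within each arm:
- 45% against 35%: (7.5²/60)·2 + 6·(1.25²/15)·2 = 1.875 + 1.25 = 3.1, p = 0.79.
- 50% against 30%: (15²/60)·2 + 6·(2.5²/15)·2 = 7.5 + 5.0 = 12.5, p = 0.052. Diagnosis would still stay out.

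**What the rule does to the estimate.** Simulation with 133 per arm, SD 25, no treatment effect, one continuous covariate, a 5% t-type baseline test and 10,000 runs. The covariate–outcome correlations are assumed.

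| Correlation | Covariate selected | SD of estimate: unadjusted | Under the rule | Always adjusted |
|---|---|---|---|---|
| 0 | 4.8% | 3.06 | 3.06 | 3.06 |
| 0.3 | 4.9% | 3.09 | 3.05 | 2.95 |
| 0.5 | 4.8% | 3.03 | 2.92 | 2.65 |

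Selection stays near 5% whether or not the covariate predicts outcome. At correlation 0.5 the rule reduces the SD by 3.03 − 2.92 = 0.11, out of 3.03 − 2.65 = 0.38 available from fixed adjustment. The nominal 5% test under the rule rejects in 4.2% of runs, which is slightly conservative.

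**The case against.** The strongest defence is that the rule has narrow reach and is written down in advance. The main model's covariates are fixed. The six candidates were listed because they may be prognostic, so clinical judgement shaped the pool and chance decides only which of them enter. The trigger uses baseline data alone and never sees outcomes. All of this stands and limits the weight of the point.

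Three stronger readings are tempting and not supported:

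- *A reader might infer that the main adjusted analysis has no fixed covariate set, or cannot do its job.* The article fixes primary problem and WHO performance score without a test. Only the added sensitivity analysis depends on the rule.
- *A reader might infer that false positives are inflated, or that covariates could be picked to suit the result.* Selection is blind to outcome, and the simulation shows slight conservatism.
- *A reader might infer that the survival and cost models are built on test-selected covariates.* The text is unclear. It can equally mean only the fixed pair.

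The sizes are also fairly challenged. The test level, the independence of the tests, the 40% prevalence and the simulated correlations are all assumptions. They set the figures, but the selection probability equals the test level under any of them.

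A separate analysis plan does not dispose of the point, because the article states the rule outright.

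**Conclusion.** The point holds, limited to the sensitivity analysis of the questionnaire data. The entry rule selects among six named variables by chance imbalance and not by prognostic strength. At an assumed level of 0.05 with independent tests there is about a 26% chance that anything is added and about a 74% chance that the analysis repeats the main model. Variables whose imbalance has a p-value above the threshold stay unadjusted even if they are strong predictors and the imbalance is material.

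The primary estimate, its type I error and the sample size of 133 (150 enrolled) per arm are unaffected. The precision shown in the simulation concerns the sensitivity model. The reach would extend to the Cox and cost models only if their reference to the questionnaire covariates includes the selected ones, which the text leaves open. The change should be made, but the trial's main conclusion does not depend on it.

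**What to change.** 1. Report baseline characteristics by arm descriptively, and drop the Wilcoxon and chi-squared tests as a way of choosing covariates.
2. Name the sensitivity-analysis covariates now, on prognostic grounds and whatever imbalance is observed: for example primary problem, WHO performance score, diagnosis, cancer stage, age and gender. Marital status and education can be kept or left out on the trial team's prior judgement, provided the decision is made before the data are seen.
3. In Survival and Economic consequences, list the covariates so that they are clearly a prespecified set.

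**Cost.** Analysis wording only; every variable is already registered at baseline. Beyond the main model, diagnosis in seven groups adds 6 terms, age 1, gender 1, and stage 1 to 3 depending on its coding (an assumption). That is 9 to 11, roughly ten, on top of 12 for the 13-level primary problem plus those for performance score. With 300 × 0.90 = 270 patients expected to contribute, this is affordable. The article reports 68% of patients enrolled and analyses still to come, so at that stage the change could precede the analysis.
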